### Follow-up phone call at Day 60 (M2)

- Evaluation of the clinical status
- Document concomitant medications
- Record any serious adverse events and all adverse events

### Early Withdrawal Visit

- Documentation of any changes in clinical examination
- Vital signs if before day 15
- Nasopharyngeal swab collection for RT-PCR SARS-Cov2 (qualitative assessment and viral load) if before day 15, after qualitative analysis, this sample will be stored at local site.
- Documentation of respiratory status: respiratory rate, oxygen supplementation, SpO2 at rest or PaO2, radiographic findings (if available)
- 8-point Ordinal scale
- Blood analysis if before day 15
- Blood sample collection (if applicable)
- Document concomitant medications
- Record any serious adverse events and all adverse events

**STUDY SCHEDULE FOR all patients in Phase 2b**

| **Activities** | 0 to 2 Days before inclusion (Screening) | D1  (Inclusion visit) | D2 | D3 | D5 **  (+/- 1 day) | D8  (+/- 1 day) | D15  (+/- 1 day) | D29  ***  (+/- 1 day) | D60  **** | Early Withdrawal |
| --- | --- | --- | --- | --- | --- | --- | --- | --- | --- | --- |
| Patient information | X |  |  |  |  |  |  |  |  |  |
| Informed Consent | X |  |  |  |  |  |  |  |  |  |
| Randomisation |  | X |  |  |  |  |  |  |  |  |
| Previous medical history | X |  |  |  |  |  |  |  |  |  |
| Clinical examination and vital signs^1^ | X | X | X | X | X | X | X | X | X | X^9:^ |
| Respiratory status^2^ | X | X | X | X | X | X | X | X |  | X |
| XAV-19 administration |  | X |  |  |  |  |  |  |  |  |
| Diagnosis of SARS-Cov-2 infection before screening, by positive SARS-CoV-2 RT-PCR or antigen (*) | X |  |  |  |  |  |  |  |  |  |
| RT-PCR SARS-Cov2 (Nasopharyngeal swab samples) | * | X^3^ |  |  |  | X^11^ | X^11^ | X^11^ |  | X^11^, ^9:^ |
| ECG |  | X | X^4^ | X^4^ | X^4^ | X^4^ | X^4^ | X^4^ |  | X^4^ |
| Serology^5^ | X |  |  |  |  |  |  |  |  |  |
| Urine pregnancy test | X |  |  |  |  |  |  |  |  |  |
| Blood analysis^6^ | X | X |  | X | X | X | X | X |  | X^9:^ |
| Pharmacokinetic^7^ |  | X^8^ |  | X | X | X | X | X |  |  |
| Transcriptomic analyses^7^ |  | X |  | X | X | X | X |  |  |  |
| Lymphocyte subpopulation^7^ |  | X |  | X | X | X | X |  |  |  |
| Cytokines^7^ |  | X |  | X | X | X | X |  |  |  |
| Spike/ACE2 neutralizing antibody titers^7^ |  | X^8^ |  | X | X | X | X | X |  |  |
| 8-point ordinal scale^10^ | X | X | X | X | X | X | X | X |  | X |
| Concomitant treatment | X | X | X | X | X | X | X | X | X | X |
| Adverse events | X | X | X | X | X | X | X | X | X | X |

* Documented positive SARS-CoV-2 RT PCR before enrolment (if screening nasopharyngeal swab sample done at study site, this sample should be stored after analysis).

**: Only if still hospitalized at Day 5, otherwise phone all. Patients participating to the ancillary studies will have to come back on site for this visit.

*** If not hospitalized Day 29 is a phone call visit except for patients participating to the ancillary studies will have to come back on site for this visit (Vital signs, Nasopharyngeal swab collection for RT-PCR SARS-Cov2 and blood analysis will be done only if visit on site).

**** if not hospitalized Day 60 is a phone call visit.

^1^: Clinical examination: Full physical examination at Day1 and brief targeted examination at other visits. Vital signs: Blood pressure, pulse rate, body temperature, Height (cm) and body weight (kg) (only at D1),.

^2^.Respiratory status: respiratory rate, oxygen supplementation, SpO2 at rest or PaO2, radiographic findings (if available). For outpatients, only supplement oxygenation will be enquired.

^3^: For viral load assessment. Not to be done if screening RT-PCR was obtained in the same study site. After qualitative analysis, nasopharyngeal swab samples to be stored at the site)

^4^: ECG: to be performed at the discretion of the Investigator, as deemed necessary for appropriate patient care

^5^: Serology: HIV, hepatitis B/C, COVID-19 (after analysis remaining serum will be stored under usual conditions at local site)

^6^: Blood analysis: **Hematology**: hemoglobin, hematocrit, red blood cell (RBC) count, white blood cell (WBC) count with differential (absolute counts and including calculation of total lymphocytes), and platelet (PLT) count.

**Serum Chemistry:** creatinine, glucose, total protein, total bilirubin, alkaline phosphatase (ALP), aspartate aminotransferase (AST), alanine aminotransferase (ALT), gamma glutamyltransferase (GGT), C-reactive protein, ferritin,

^7^: Only for patients participating in the ancillary studies

^8^: Immediately before administration and at the end of infusion

^9:^ done only if before day 15

^10^: assessed daily

^11^: For viral load assessment. After qualitative analysis, nasopharyngeal swab samples to be stored at the site)

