**Clinical severity**:

a) National Early Warning Score (NEWS) over 29 days:

*-* Change from baseline to Day 3, 5, 8, 15 and 29

- Time to discharge or a NEWS <=2 and maintained for 24 hours

b) 8-point ordinal scale over 29 days

- Time to improvement of one category from baseline (Day 1)

- Mean change in ordinal scale from baseline to Day 3, 5, 8, 15 and 29

- Percentage of subjects reporting each severity rating on an 8-point ordinal scale at Day15

c) Improvement of clinical and biological parameters over Day 15

d) Oxygenation

- Duration of oxygen therapy over 29 days

- Time to weaning in supplemental oxygen

- Proportion without O2 requirement at D8, D15 and D29

e) Non-invasive ventilation, high-flow oxygen

*-* Non-invasive ventilation/high flow oxygen use up to Day 29

- Incidence and duration of non-invasive ventilation or high flow oxygen use during the study

- Time to first day with non-invasive ventilation/high flow oxygen

f) Invasive mechanical ventilation / Extra Corporeal Membrane Oxygenation (ECMO)

- Ventilator / ECMO use up to Day 29

- Incidence and duration of new mechanical ventilation or ECMO use during the study

- Time to first day with Invasive Mechanical Ventilation / extracorporeal membrane oxygenation

g) Transfer to ICU by Day 29

h) Hospitalization

- Hospital length of stay (in days)

i) Mortality

- Mortality rate at day 15 and at Day 29 and at Day 60

j)Thrombotic events

-°cumulative incidence of thrombotic events : venous, pulmonary embolism, arterial thrombotic events.

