### Visit on Day 5 (if still hospitalized)

- Documentation of any changes in clinical examination
- Vital signs
- Documentation of respiratory status: respiratory rate, oxygen supplementation, SpO2 at rest or PaO2, radiographic findings (if available)
- 8-point Ordinal scale
- Document concomitant medications
- Record any serious adverse events and all adverse events
- Blood analysis
- Blood sample collection (if applicable):
  - - Pharmacokinetic sample
    - Spike/ACE2 interaction neutralizing antibody sample
    - Lymphocytes subpopulation
    - Cytokines
    - Transcriptomic analyses

If patients are discharged from hospital before Day 5, patient will not come on-site for the Day 5 visit, this will be done via a phone call, except if patient is participating to the ancillary studies, in which case patient will have to come on site for this visit.

### Visits on Day 8, Day 15

- Documentation of any changes in clinical examination
- Vital signs
- Nasopharyngeal swab collection for RT-PCR SARS-Cov2 (qualitative assessment and viral load), after qualitative analysis, this sample will be stored at local site.
- Documentation of respiratory status: respiratory rate, oxygen supplementation, SpO2 at rest or PaO2, radiographic findings (if available)
- 8-point Ordinal scale
- Blood analysis
- Blood sample collection (if applicable):
  - - Pharmacokinetic sample (for the first 20 patients included in this ancillary study, for following patients the PK analysis will be done from immunology blood samples ; and for the 20 patients of the terminal ancillary study)
    - Spike/ACE2 interaction neutralizing antibody sample
    - Lymphocytes subpopulation
    - Cytokines
    - Transcriptomic analyses
- Document concomitant medications
- Record any serious adverse events and all adverse events

If patients are discharged from hospital before Day 8, patient will have to come back on-site for the Day 8 and Day 15 visits.

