**The other secondary endpoints are:**

1. National Early Warning Score (NEWS) assessed while hospitalized and on Day 15 and Day 29
2. Clinical status using the 8-point ordinal scale assessed daily until Day 29
3. Temperature and blood analysis between baseline and Day 15, and Day 29
4. Days of oxygen therapy over 29 days

PaO2 / FiO2 at baseline, Day 5, Day 8, Day 15, Day 29 if available

1. Days of non-invasive ventilation or high flow oxygen (if applicable) up to Day 29
2. Days of invasive mechanical ventilation/ECMO (if applicable) up to Day 29
3. Transfer in ICU
4. Hospital length of stay (in days)
5. All-cause mortality evaluated between baseline and Day 15 and between baseline and at Day 29 and at Day 60
6. Thrombotic events (peripheral venous, pulmonary, arterial)

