### NEWS score (version 2)

NEWS score is an early warning score developed for monitoring hospital in-patients over time using repeated measures.

NEWS has demonstrated an ability to discriminate subjects at risk of poor outcomes.

This score is based on 7 clinical parameters.

Reference: https://www.cebm.net/covid-19/should-we-use-the-news-or-news2-score-when-assessing-patients-with-possible-covid-19-in-primary-care.

The NEWS is based on a simple aggregate scoring system in which a score is allocated to physiological measurements. Six simple physiological parameters form the basis of the scoring system:

- respiration rate
- oxygen saturation
- systolic blood pressure
- pulse rate
- level of consciousness or new confusion
- temperature.

The score is then aggregated and uplifted by 2 points for people requiring supplemental oxygen to maintain their recommended oxygen saturation.

[figure not shown]

This should be evaluated at the first assessment of a given study day and prior to administration of study product. The 7 parameters can be obtained from the hospital chart using the last measurement prior to the time of assessment and a numeric score given for each parameter (e.g., a RR of 9 is one point, oxygen saturation of 92 is two points).

This score takes into account hypercapnic respiratory failure over time, using scale 2 for Sp02.

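### Footnote 2 of the phase 2b flow chart conflicts with the on-site Day 8 and Day 15 visit text; where it is followed literally, NEWS at those visits exists only for patients still in hospital

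*Combined protocol and SAP*

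**What the plan says.** **Flow chart.** In the phase 2b schedule (Protocol 6.2), footnote 2 is attached to the label of the respiratory status row, so it applies to every marked column, Day 8 and Day 15 included. After listing the measurements it adds: "For outpatients, only supplement oxygenation will be enquired".

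**Visit text.** Protocol 6.2.6 (Day 8 and Day 15) lists "Documentation of respiratory status: respiratory rate, oxygen supplementation, SpO2 at rest or PaO2, radiographic findings (if available") with no exception for discharged patients. For those discharged before Day 8 it states: "patient will have to come back on-site for the Day 8 and Day 15 visits". Protocol 6.3 gives the same full definition of respiratory status, again without exception.

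**NEWS.** Protocol 3 and SAP 1.3 name as a secondary endpoint "National Early Warning Score (NEWS) assessed while hospitalized and on Day 15 and Day 29". The matching objective in Protocol 3 and SAP 1.2 is "Change from baseline to Day 3, 5, 8, 15 and 29". SAP 5.1 says of the score: "Six simple physiological parameters form the basis of the scoring system". Respiration rate and oxygen saturation are two of the six, and two points are added for supplemental oxygen.

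**The concern.** A discharged patient who attends the clinic on Day 8 or Day 15 is an outpatient. On the wording of the footnote, staff would ask that patient about oxygen and record nothing else under respiratory status. On the wording of 6.2.6, they would also measure respiratory rate and SpO2. The two instructions cannot both be followed.

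What is at stake is which patients have a NEWS. If the footnote is followed, only those still in hospital can be scored. Being in hospital on Day 8 or Day 15 is a consequence of the course of disease after randomisation and may depend on treatment. An arm comparison of NEWS level or change would then be made in a set selected on outcome, with the recovered patients absent. Respiratory rate and SpO2 not measured at the visit cannot be recovered afterwards.

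**Working it through.** **1. Are discharged patients on site?** Yes. Protocol 6.2.6 says so for discharge before Day 8. The chart provides a phone contact only at Days 5, 29 and 60, so Day 15 is on site for later discharges too.

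**2. Which NEWS components would be available for a discharged patient at Day 8 or Day 15?**

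| Component | Source | Visit text followed | Footnote followed literally |
| --- | --- | --- | --- |
| Respiration rate | Respiratory status | Yes | No |
| Oxygen saturation | Respiratory status | Yes (SpO2, or PaO2 recorded instead) | No |
| Systolic blood pressure | Vital signs | Yes | Yes |
| Pulse rate | Vital signs | Yes | Yes |
| Consciousness | Vital signs (Protocol 6.3) | Yes | Yes |
| Temperature | Vital signs | Yes | Yes |
| Supplemental oxygen (+2) | Oxygen question | Yes | Yes |

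Under the footnote, 2 of 6 parameters are missing and the score cannot be completed.

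**3. Is there a fallback?** None was found. The phase 2b chart has no NEWS row. SAP 5.1 names one source: "The 7 parameters can be obtained from the hospital chart using the last measurement prior to the time of assessment", which does not serve a patient who has gone home. SAP 5.4 has no rule for a missing NEWS value.

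**4. How many patients?** The plan gives no figure for this. Its nearest figure is the sample size, which reproduces. For 20% versus 10%, two-sided 5%, 80% power and pooled variance, n per arm = [1.960 × √(2 × 0.15 × 0.85) + 0.842 × √(0.16 + 0.09)]² / 0.10² = 199, so 398 in total.

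Let d be the share discharged by Day 15 and s the share of those patients at sites that follow the footnote literally. Then Day 15 scores lost = 398 × d × s. Neither d nor s is in the documents.

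- s = 0: none lost, whatever d is.
- s = 1, d = 0.50 (assumed): 398 × 0.50 = 199.
- s = 1, d = 0.85 (assumed): 398 × 0.85 = 338.

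The range 199-338 is therefore an upper bound within the assumed discharge range. It also counts every discharged patient as attending. The Day 8 figure would be no larger, since cumulative discharge by Day 8 cannot exceed that by Day 15.

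**5. Which analyses need a NEWS after discharge?**

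- Primary and key secondary endpoints: no. They use death and respiratory support (SAP 1.3, 5.1).
- Time to discharge or NEWS ≤ 2: no. Discharge is itself an event (SAP 5.1).
- NEWS level and change by visit: yes. SAP 5.2 summarises these by arm at each study visit.

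**The case against.** A reader might infer that the footnote overrides the visit text, so that the Day 15 NEWS cannot be scored after discharge. The documents do not support that.

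- Nothing gives the footnote precedence. Protocol 6.2 describes the flow chart as a summary, and the detailed text in 6.2.6 and 6.3 requires both measurements.
- A phone-only reading is the more natural one. The footnote speaks of asking, not measuring. Discharged patients outside the ancillary studies are phoned at Day 5 and Day 29. The chart note on Day 29 restricts vital signs, swab and blood analysis to on-site visits but does not mention respiratory status, and footnote 2 would fill that gap. In the phase 2a chart for the last six patients at 2 mg/kg, the counterpart restriction is marked only on Days 4, 6, 7, 11 and 13, which become phone visits after discharge, and not on Day 8 or Day 15.
- The consequence is limited. SAP 5.2 gives NEWS level and change descriptive summaries only. A formal comparison could come only from the general mixed-model sentence for quantitative endpoints in Protocol 7.2.1. SAP 3.1 treats all secondary objectives as exploratory.
- There is a firmer NEWS gap elsewhere. At Day 29, a named endpoint day, discharged patients outside the ancillary studies are only phoned, so NEWS cannot be scored on either reading. The same holds at Day 5 for the change objective.

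All of this stands, and it rules out a claim of certain loss. It does not remove the conflict. The same chart writes explicitly of phone calls and on-site visits in its other notes, whereas footnote 2 refers to outpatients and covers the whole row. The day-specific marking used in phase 2a was not carried over. Sites could reasonably apply the note in different ways. The Day 5 and Day 29 gap is a separate matter; it makes Day 8 and Day 15 the only visits at which NEWS can be measured after discharge in all attending patients.

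**Conclusion.** The conflict is real and unreconciled. Where the footnote is followed literally, NEWS level and change at Day 8 and Day 15 are available only for patients still in hospital, and the missingness is informative. Where 6.2.6 is followed, nothing is lost.

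The size cannot be determined from the documents. The upper bound of about 199-338 of 398 at Day 15 rests on two assumptions: that 50-85% are discharged by then, and that every site follows the footnote. It is not an expected loss. The effect is confined to an exploratory secondary outcome and does not touch the primary endpoint, the key secondary endpoints, or time to discharge or NEWS ≤ 2. The correction is worth making because it is simple and the data, if missed, cannot be retrieved.

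**What to change.** Reconcile footnote 2 with Protocol 6.2.6 and 6.3 by limiting it to phone contacts, for example: *For phone contacts, only supplemental oxygen will be asked.* Respiratory rate and SpO2 would then be recorded at on-site Day 8 and Day 15 visits, as 6.2.6 already states. Have the eCRF collect all NEWS components at those visits.

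Two small additions would help: a NEWS row in the phase 2b chart, and a sentence in SAP 5.4 on how a missing NEWS is handled.

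The cost is one line in the chart plus eCRF fields. No measurement is added beyond what the visit text already requires, at visits that already take vital signs and blood.

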## Procedures details

All examinations are performed by the investigator or a qualified member of the investigational staff.

- All inclusion and exclusion criteria will be reviewed prior to patients entering the study

- Informed consent form will be signed prior to any specific study procedure.
- Medical History: including COPD and chronic respiratory insufficiency, and if applicable, assessment of their severity.
- The full physical examination includes the following assessments will be done: Cardiovascular, Head-Ear-nose-throat, Eyes, Gastro-intestinal, General Appearance, Lymph nodes, Musculoskeletal, Neurological, Respiratory, Skin and Mucous Membranes. Body weight and height will be measured.

Any abnormalities present at Inclusion, or subsequent changes, will be documented in the appropriate sections of the eCRF. Any clinically significant abnormalities persisting at the end of the study will be followed by the investigator until resolution or until reaching a clinically stable endpoint.

- Vital signs include: Blood pressure, pulse rate and body temperature will be taken at each assessment per the Study Schedule. Height (cm) and weight (kg) will be taken only at screening. Blood pressure and pulse will be taken after the patient has been resting in supine position for 5 minutes. Level of consciousness will also be assessed.
- Respiratory status: respiratory rate, oxygen supplementation, SpO2 at rest or PaO2, radiographic findings (if available).
- Electrocardiogram (ECG):

The 12-lead digitalized ECGs will be recorded according to the Study Schedule while the patient is in supine position for at least 5 minutes. ECG is performed at inclusion visit, other ECG will be performed at the discretion of the Investigator, as deemed necessary for appropriate patient care.

- Blood analyses and serology:

Blood samples for serum chemistry and haematology will be collected according to the Study Schedule. In addition, a urine sample for women of childbearing potential for pregnancy testing will be collected at screening to confirm eligibility criteria (in case as per local site practice pregnancy testing is done on blood sample, no additional urine sample is needed and the blood pregnancy testing result will be collected). The investigator must review the laboratory report, document this review, and record any clinically relevant changes occurring during the study in the adverse event section of the eCRF.

Results of serological tests performed prior to the subject signing consent as part of routine clinical management is acceptable in lieu of a screening test.

***Serum Chemistry***

- creatinine,
- urea*,
- glucose,
- total protein,
- phosphorus*,
- bicarbonate*,
- total bilirubin,
- direct and indirect bilirubin*,
- alkaline phosphatase (ALP),
- aspartate aminotransferase (AST),
- alanine aminotransferase (ALT),
- gamma glutamyltransferase (GGT),
- sodium (Na)*,
- potassium (K)*,
- chloride (Cl)*,
- albumin*,
- creatine kinase (CK)*,
- lactate deshydrogenase (LDH)*,
- lipase*

***Haematology:***

- hemoglobin,
- hematocrit,
- red blood cell (RBC) count,
- white blood cell (WBC) count with differential (absolute counts and including calculation of total lymphocytes),
- platelet (PLT) count

***Serology (remaining serum after analysis will be stored under usual conditions at local site):***

- HIV,
- hepatitis (B & C),
- COVID-19

***Inflammatory markers and cytokines***

- C-reactive protein (CRP)
- Ferritin
- D-dimers*
- IL-6* (if available locally)
- Procalcitonin* (if available locally)

***Urine analysis (by stick)*** ****:***

- Proteinuria

* Only for Phase 2a

All of these blood and urine analysis will be performed locally by each center.

- Pharmacokinetic analysis:

Blood sample (3,5mL) will be collected at each draw for specific analysis as described below according to the Study Schedule

These analyses will be performed a R&D grade locally in order to provide data to the DSMC. Final data will be obtained from Citoxlab/Charles Rivers and run under GLP conditions.

In the phase 2a all patients included in the study will have pharmacokinetic samples taken.

- Immunological analyses on blood sample:

Blood sample will be collected for specific analysis as described below according to the Study Schedule. Actual time and date of blood drawn must be accurately recorded on the eCRF.

The following analyses will be performed:

-T and B lymphocyte subpopulations

-Spike/ACE2 interaction neutralizing antibody.

-Serum cytokines: MCP1, IP10, IL-10, IFNa, TNF-α, IL-1b, IL-6, IL-82 (in the phase 2a) and IL-6, IFNa2, IL-10, IP10, CCL2 (in the phase 2b).

These analyses will be performed by the CIMNA/Nantes University Hospital.

- Transcriptomic analyses

Messenger RNA molecules will be extracted from peripheral blood in order to identify transcripts that are specifically over- or under-expressed in correlation with the clinical status and with viral load. The goal is to identify possible biomarkers of the disease severity and disease responding to the treatment, and, using deconvolution bioanalyses, also identifying cell population changes in complement to the direct flow cytometry analyses. A focus will be made on B cell subpopulation and their role in interaction with Tfh cells.

These immunological analyses will be performed by the CRTI in Nantes University (INSERM U1064) (lead by [name], CNRS).

During the study, including the end-of-study visit, the total blood volume to be collected from each patient specific for the research analyses will be 253mL (1).

These estimates are for required additional blood samples specific for the study and do not include additional blood samples that may be collected at the investigator’s discretion for drug level monitoring or other clinical laboratory tests deemed necessary for appropriate patient care in case of occurrence of adverse events.

| Table 1: Estimated Blood Volume Drawn specific to the study: | | | |
| --- | --- | --- | --- |
| **Type of Sample** | **Volume per Sample (mL)** | **No. of Samples per Patient** | **Total Volume of Blood  (mL)^a^** |
|  |  |  |  |
| PK  Lymphocyte sub-population and cytokine | 3,5  5 | 8 (7)  5 | 28 (24.5)  25 |
| Spike/ACE2 neutralizing antibody titers | 5 | 8 (7) | 40 (35) |
| Transcriptomic | 50 | 5 | 200 |
| Total blood volume drawn |  |  | 293 (284.5) |
| ^a^ Calculated as number of samples multiplied by amount of blood per sample.  (x) If only one treatment administration at D1 | | | |

- Nasopharyngeal swab samples will be used to perform RT-PCR in order to detect SARS-CoV-2, and collect information (D1 or screening sample) on presence or not of variant. These samples should be stored after analysis at the site for further analysis at central laboratory (viral load).
- Ordinal scale:

The ordinal scale is an assessment administered by the investigator to determine the clinical status of the patient, the scale is as follows:

The 7-point ordinal scale (Phase 2a)

1. Not hospitalized, no limitations on activities;

2. Not hospitalized, limitations on activities;

3. Hospitalized, not requiring supplemental oxygen;

4. Hospitalized, requiring supplemental oxygen;

5. Hospitalized, on non-invasive ventilation or high flow O2 devices;

6. Hospitalized, on invasive mechanical ventilation or ECMO;

7. Death.

The 8-point ordinal scale (<https://www.who.int/blueprint/priority-diseases/key-action/COVID-19_Treatment_Trial_Design_Master_Protocol_synopsis_Final_18022020.pdf>) (Phase 2b)

[figure not shown]

The ordinal scale of the clinical status will be assessed daily until Day29. Each day, the worse score for the previous 24 hours will be recorded. i.e. on day 3, day 2 score is obtained and recorded as day 2.

On Day 1, assessment will have to be performed before IMP infusion.

- National Early Warning Score (NewS2) (<https://www.cebm.net/covid-19/should-we-use-the-news-or-news2-score-when-assessing-patients-with-possible-covid-19-in-primary-care/>):

The NEWS is based on a simple aggregate scoring system in which a score is allocated to physiological measurements. Six simple physiological parameters form the basis of the scoring system:

- respiration rate
- oxygen saturation
- systolic blood pressure
- pulse rate
- level of consciousness or new confusion
- temperature.

The score is then aggregated and uplifted by 2 points for people requiring supplemental oxygen to maintain their recommended oxygen saturation.

[figure not shown]

PaO2/FiO2 Ratio (EPICII conversion table8 May 2007)
[figure not shown]

[figure not shown]

- Concomitant treatments

Concomitant treatments will be reported for the duration of the study. Concomitant treatments will be reported in the eCRF

- Adverse Events

Adverse events will be reported for the duration of the study from the signature of the informed consent form until the end of the study. Adverse events will be followed by the investigator as specified in Section 8, and reported in the eCRF.

